##### Blinding

As this is an open-label study and it is impossible to blind participants and the peer navigator. Only the data analysts will be blinded (we are using electronic data and an objective measurement -HOMA-IR score) so unblinding will not occur.

##### Provision of ancillary and post-trial care

Participants in the intervention have no greater than minimal risk. There is no anticipated harm or compensation for harm. Any incidental clinical finding will be reported to the participant, if appropriate, and their clinic provider. Participants will maintain regular clinical care post-trial.

##### Process data collection

We will also conduct process evaluation to document intervention delivery. The peer navigator will maintain a log in REDCap of their interactions with weCare/Secure participants to capture the mode of intervention delivery, dose, and messaging for each participant (e.g., which mHealth platforms were used, who initiated contact [the participant or peer navigator], the dates and times that messages were sent, number of messages exchanged, and the types of messages utilized to communicate with each participant).

##### Power and sample size for Aim 2

Assuming 100 participants are randomized to the intervention arm and 100 to the usual care arm, we will have 80% power to detect a difference in the mean change in HOMA-IR between arms of 0.54, assuming a standard deviation of 1.5 (based on unpublished data from our clinic) and a correlation of 0.6 between baseline and follow-up assessments.

##### Analysis plan for Aim 2

We will use a longitudinal RCT with 2 arms (intervention and usual care) to evaluate the impact of the intervention. Data will be analyzed as an intent-to-treat study [60]; with electronic health data, we do not expect much missing data (at any of the time points) so we do not plan to use data imputation techniques. First, we will compare the characteristics of participants assigned to the intervention and usual care arms using *t-*tests for continuous covariates and *χ*^2^ tests for discrete covariates. Our primary data analysis will compare mean HOMA-IR levels for the intervention and usual care arm participants at the 6-month follow-up assessment adjusting for baseline levels. This follow-up adjust baseline approach has the advantage of being unaffected by baseline differences. If baseline rates, by chance, were different in the intervention arm, the intervention effect would be overestimated by looking at change scores and underestimated by a follow-up score analysis. The ANCOVA approach gives the same answer whether or not there is baseline imbalance. Additionally, this approach generally has greater statistical power to detect an intervention effect than the other methods. Statistical analyses will be performed using linear models for continuous outcomes in SAS PROC GLM.

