#### Aim 2: Implement and test weCare/Secure to determine the impact of the intervention on insulin sensitivity among food-insecure PWH with prediabetes or T2DM using an RCT

##### Participants

The participants in Aim 2 will be a subset of Aim 1 participants who enrolled in year 1. From potentially eligible participants identified by EHR data extracted in Aim 1, we will randomly select participants to invite to enroll in Aim 2, starting in year 2. To be eligible to participate in Aim 2, a participant must (a) be a patient of the Wake Forest Infectious Diseases Specialty Clinic, (b) be living with HIV, (c) be receiving antiretroviral therapy (ART) for ≥ 3 months, (d) be ≥18 years of age, (e) screen as food insecure, (f) have prediabetes or T2DM, and (g) provide informed consent. Access to a smartphone will not be an inclusion criterion because participants may communicate with the peer navigator via mHealth platforms accessible on a computer (e.g., Facebook messenger) at their home or in community spaces such as the public library. PWH will be excluded if they are unable to speak English or Spanish, are currently pregnant, are receiving chronic treatment with systemic corticosteroids (similar exclusion as the Look AHEAD Trial, which evaluated the effects of an intervention designed to promote weigh loss among overweight and obese individuals with T2DM [57]), have type 1 diabetes, and/or have cognitive impairment that would prevent participation.

If participants are eligible and consent to participate, they will then complete Aim 2 baseline data collection as outlined in Table 1. After these data are collected, they will be randomly assigned into weCare/Secure (*n*=100) or usual care (*n*=100). Those randomized to the weCare/Secure intervention will receive the intervention for 6 months. For random selection and assignment, our statistician will use block randomization with a randomly selected block size. The research coordinator will enroll, consent, and assign participants to groups. We will continue this process until we reach our sample size of 200. Participants may discontinue participation in the intervention at any time. Given the behavioral nature of the intervention, there will be no other special criteria for discontinuing or modifying allocated interventions. Aim 2 participants will be compensated $40 at baseline and $60 at 6-month follow-up.

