##### Data collection

The quantitative assessment will collect demographic, cognitive, behavioral, psychosocial, and socioeconomic data at baseline and post-intervention follow-up using REDCap (Research Electronic Data Capture), a secure web application for building and managing online surveys and databases maintained by Wake Forest University School of Medicine. Selection of other constructs are guided by the underlying theories and literature describing factors influencing food insecurity and cardiometabolic comorbidities (as highlighted in Fig. 1).

Table 1 provides measurement priorities identified while preparing the application for this study. The assessment, including final selection of measures, will be created using an iterative process by the research team in collaboration with a project-specific community steering committee comprised of community members (including PWH) and representatives from community organizations that provide services related to HIV and to food security. The assessment will be translated into Spanish by a native Spanish speaker trained in professional translation. Participants will complete the quantitative assessment on a tablet while attending baseline and post-intervention (6 months post-baseline) study visits at the clinic.

Our primary outcome for Aim 2 is the difference in mean difference homeostatic model assessment of insulin resistance (HOMA-IR) score between intervention and control arm participants at 6 months, controlling for baseline HOMA-IR is capable of measuring small changes in insulin sensitivity, especially among PWH and persons with prediabetes [58, 59]. At each study visit, fasting glucose and fasting insulin levels will be measured to calculate participants’ HOMA-IR score by venous blood sample. The blood sample will not be stored for future use.

For our secondary outcomes, we will assess for change in food security and change in the pathways (nutrition, mental health, and behavioral; Fig. 2) proposed to influence food insecurity and cardiometabolic comorbidities from baseline to 6-month follow-up (Table 1). To measure the change in food security over a 6-month period, we will use the 18-item USDA Food Security Survey Module (FSSM) 30-day questionnaire, in addition to the 2-item Hunger Vital Sign assessment. The 30-day questionnaire assesses food insecurity over the prior month and successfully assesses changes in food security over time [53, 54].

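### Aim 2 leaves prediabetes v T2DM status out of the primary model: no bias follows, but precision may be given away that one pre-specified covariate would recover

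*Protocol article*

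**What the plan says.** The eligibility list for Aim 2 (Protocol article, Aim 2, Participants) requires that a participant "f) have prediabetes or T2DM, and (g) provide informed consent". The definitions are given under Aim 1, Data collection. Prediabetes is an A1C from 5.7% to below 6.5%. T2DM is an A1C of 6.5% or more, a diagnosis code, or current use of a diabetic medication, with insulin on the list. Because status is an entry criterion and baseline data are collected before assignment, it is known for everyone at randomisation.

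Participants are then "randomly assigned into weCare/Secure (*n*=100) or usual care (*n*=100"). For the method, "our statistician will use block randomization with a randomly selected block size". No stratification factor is named.

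Under Analysis plan for Aim 2, the primary analysis compares mean HOMA-IR in the two arms' "participants at the 6-month follow-up assessment adjusting for baseline levels". The software sentence reads "Statistical analyses will be performed using linear models for continuous outcomes in SAS PROC GLM". Baseline HOMA-IR is the only covariate named. The same paragraph defends the method as untouched by baseline differences and as giving one answer with or without baseline imbalance, and it does not limit that claim to HOMA-IR.

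Under Power and sample size for Aim 2, the article states that "we will have 80% power to detect a difference in the mean change in HOMA-IR between arms of 0.54". The inputs it gives are an SD of 1.5, drawn from the clinic's own unpublished records, and a baseline to follow-up correlation of 0.6.

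**The concern.** Prediabetes and T2DM are different glycaemic states, and the T2DM group includes people on glucose-lowering drugs. HOMA-IR is calculated from fasting glucose and fasting insulin, so the label may track treatments that act on the outcome's own components. Disease type could then carry information about 6-month HOMA-IR that baseline HOMA-IR does not.

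If so, a model without disease type leaves explainable variance in the residual. What is at stake is efficiency: a wider confidence interval than these 200 participants could give. The article's defence of ANCOVA also reads more broadly than it should, because adjustment removes the effect of imbalance only in the variable adjusted for.

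**Working it through.** **Inputs from the article:** 100 per arm, SD 1.5, correlation 0.6, difference 0.54, power 80%. **Assumed:** two-sided 5% level (the Aim 2 power paragraph states none), no dropout, share p of T2DM, and g, the difference in 6-month HOMA-IR between disease types that remains after baseline HOMA-IR. The total residual SD without disease type is held at the value the article implies.

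**1. Reproduce the stated power.** The detectable difference is (1.960 + 0.842) × SD × √(2/100).
- Change score: SD = 1.5 × √(2 × (1 − 0.6)) = 1.342. The detectable difference is 0.532, and power at 0.54 is 0.81. This matches the article's figure.
- ANCOVA, the planned analysis: SD = 1.5 × √(1 − 0.36) = 1.2. The detectable difference is 0.475, and power at 0.54 is 0.889.

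The article's figure is therefore a change-score calculation and is conservative for the planned model.

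**2. Add disease type to the ANCOVA.** Residual variance falls from 1.44 to 1.44 − p(1 − p)g². The effective-sample gain is 1.44 / (1.44 − p(1 − p)g²) − 1. At p = 0.5:

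| g (assumed) | residual SD | detectable difference | power at 0.54 | effective-sample gain |
|---|---|---|---|---|
| 0 | 1.200 | 0.475 | 0.889 | 0% |
| 0.25 | 1.193 | 0.473 | 0.892 | 1.1% |
| 0.5 | 1.174 | 0.465 | 0.902 | 4.5% |
| 0.75 | 1.140 | 0.452 | 0.918 | 10.8% |
| 1.0 | 1.091 | 0.432 | 0.938 | 21.0% |

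As an example, at g = 1.0 the residual variance is 1.44 − 0.25 = 1.19, and 1.44/1.19 = 1.21. At a 30:70 split the gain runs from 0% to 17%.

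**3. Is chance imbalance a separate harm?** The SD of the between-arm difference in T2DM share at p = 0.5 is √(0.25 × 2/100) = 7.1 percentage points. At g = 1.0 this adds 0.25 × 1.0² × 0.02 = 0.005 to the variance of the contrast. The ANCOVA variance without disease type is 1.44 × 0.02 = 0.0288. The ratio 0.005/0.0288 = 17.4% is exactly the share of residual variance that the covariate removes (0.25/1.44 = 17.4%). Imbalance and lost precision are thus one quantity, already counted in the standard error.

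**4. Check by simulation.** There were 20,000 null trials for each g at p = 0.5, with a 100/100 permutation standing in for random blocks. Without disease type in the model, the mean estimate was −0.0007 for both values of g, and type I error was 0.048 (g = 0.5) and 0.050 (g = 1.0). Adding disease type reduced the SD of the estimate from 0.1696 to 0.1664 (g = 0.5) and from 0.1691 to 0.1541 (g = 1.0). The variance ratios are (0.1696/0.1664)² = 1.04 and (0.1691/0.1541)² = 1.20, close to the formula.

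**The case against.** The strongest reply is that the article is a condensed account. It does not say that randomisation is unstratified or that no further term enters the model, and a full protocol or SAP may name both. Baseline-adjusted ANCOVA with random blocks is a valid, standard design. Both quantities behind any gain, the disease share and the residual difference, are assumed, and at a residual difference of 0 to 0.25 the gain is 0% to 1.1%. All of this stands, and it is why the point is an efficiency recommendation and not an error. It does not remove the point, because the article fixes a named model and defends it with a claim about baseline imbalance that is wider than that model supports.

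Three stronger readings are tempting, and the documents support none of them.

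- A reader might infer that an uneven T2DM share distorts the result. Over repeated randomisations it does not: steps 3 and 4 show no bias and no loss of error control.
- A reader might infer that the trial is thinly powered and needs the covariate. On the article's own inputs the planned ANCOVA already exceeds its 80% target at 0.54. Even with 15% lost (85 per arm) its power would be 0.835.
- A reader might take the remark under Aim 2, Data collection, that HOMA-IR is "capable of measuring small changes in insulin sensitivity, especially among PWH and persons with prediabetes" as evidence that disease type is prognostic. It concerns how responsive the measure is. It also names PWH, which is every participant, so it does not separate the two groups.

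Nor does the correlation of 0.6 settle the matter. It leaves 64% of follow-up variance unexplained by baseline, but that remainder may be within-person or assay variation and need not relate to disease type.

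**Conclusion.** The point holds as a low-cost efficiency improvement. The primary analysis is valid as written, and the stated power is sound and conservative. What may be lost is precision, and only if disease type, or the treatment that goes with it, predicts 6-month HOMA-IR after baseline HOMA-IR. For an assumed residual difference of 0 to 1.0 at a 50:50 split, the loss is equivalent to between 0% and about 21% of the effective sample. This size rests on the assumed split and residual difference, a residual SD of 1.2 derived from the article's inputs, a two-sided 5% level and complete follow-up. Separately, the statement that the ANCOVA answer does not depend on baseline imbalance is correct for baseline HOMA-IR only, and should say so.

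**What to change.** - Name qualifying disease status (prediabetes v T2DM, as established at Aim 2 entry) as a pre-specified covariate beside baseline HOMA-IR in the primary PROC GLM model.
- If allocation has not started, stratify the block randomisation by the same factor. If it has started, add the covariate alone, fixed before outcome data are examined by arm.
- Reword the justification in Analysis plan for Aim 2 so that protection against baseline imbalance is claimed for baseline HOMA-IR only.

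The cost is one model term (one degree of freedom, leaving 196 instead of 197 with 200 completers) and a second block list, which may leave the arms slightly off 100/100. No new data or participants are needed. If disease type turns out to add nothing, the loss is negligible. Pre-specifying it also avoids a later choice of covariates driven by the planned baseline comparison tests.

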#### Aim 3. Advance our understanding of how weCare/Secure can most effectively improve the management and treatment of cardiometabolic comorbidities among food-insecure PWH

##### Participants

The interview participants in Aim 3 will be a subset of Aim 2 participants and recruited from three groups of Aim 2 intervention participants: (a) participants who reduced both food insecurity and increased insulin sensitivity (*n* = 15); (b) participants who either reduced food insecurity or improved insulin sensitivity (but not both; *n* = 15); and (c) participants who did not reduce food insecurity or improve insulin sensitivity (*n* = 15). Participants will be randomly selected by group. The sample size of 45 interview participants should be adequate to reach thematic saturation across these groups, but we will have flexibility to expand this sample if warranted. We will purposely recruit a diverse sample by age, time since HIV diagnosis, gender, race/ethnicity, sexual orientation, and home address (urban or rural). Aim 3 participants will be compensated $50 for their time.

##### Data collection

After the 6-month follow-up, we will conduct interviews to advance our understanding of how the intervention can improve management of cardiometabolic comorbidities with PWH. A semi-structured interview guide will be designed to assess the strengths and weaknesses of the intervention, understand participant experiences, contextualize the intervention’s impact, identify lessons learned, guide any intervention revisions, and inform future research directions. It also will focus on how the intervention affected the three pathways outlined in Fig. 2, and how interventions to address food insecurity in clinics caring for PWH can most effectively be tailored. Using the same process as above, the interview guide will be translated into Spanish.

##### Analysis plan for Aim 3

The interviews will be digitally recorded and professionally transcribed (and translated if in Spanish), with identifying data removed. Analyses will be guided by the constant comparison method, informed by grounded theory methodologies [61, 62]. This approach is well suited for systematically uncovering participant experiences and comparing them within and across groups (e.g., age, time since HIV diagnosis, gender, race/ethnicity, sexual orientation, and urban/rural). Analytic steps will include the following: after each interview, interviewers will document field notes including emerging topic areas for subsequent exploration; transcripts and field notes will be entered into Atlas.ti qualitative data management software (Berlin, Germany) for coding and analysis; we will develop a preliminary codebook to include pre-determined deductive codes related to the 3 domains (nutrition, mental health, and behavioral) and inductive codes that emerge from the data; coding differences will be discussed and negotiated in team meetings until consensus is reached; similarities and differences across transcripts will be examined and themes developed accordingly; and we will “member check” themes with the steering committee to refine and establish the validity of the results. From this rich dataset, we will develop a conceptual understanding of how interventions to address food insecurity can most effectively improve cardiometabolic comorbidities among PWH.

## Monitoring

### Steering committee

The study will be conducted by the study investigators who will be responsible for all aspects of the local organization including identifying potential participants and obtaining consent. The trial steering committee is comprised of clinic staff, and racially/ethnically and gender-diverse PWH, including individuals at risk for food insecurity and those living in rural areas. Given the diversity of the clinic, it is critical to ensure that we obtain a broad range of perspectives throughout this process. The trial steering committee will meet monthly for the first year of this study and quarterly thereafter to provide guidance on mHealth messages, measurement, recruitment and retention, and interpretation of findings.

### Data Safety and Monitoring Board (DSMB)

The DSMB will be comprised of five external researchers and a representative from a local food pantry. The DSMB will provide another mechanism to ensure the safe conduct of the study and provide additional scientific guidance. This DSMB will meet at least once annually, and more often as needed either in person or virtually to audit trial conduct.

On an ongoing basis, adverse events or complaints about the study will be reported to the study team and the DSMB. Given the behavioral nature of the intervention, serious adverse events are not anticipated; any serious adverse events and/or unanticipated problems involving risks will be reported to the DSMB, institutional officials, and sponsor as required by the protocol and federal regulation. The Principal Investigators will convene the DSMB if any member regards any adverse event as serious enough to discuss and any patterns of complaints or concerns expressed by participants. Follow-up options for adverse events include the following: (a) DSMB members will determine that the event(s) are serious enough to recommend immediate discontinuation of the study. In this case, all ongoing study participants will be notified as soon as possible of the study termination. Such notification will be initiated within 24 h of the DSMB decision; (b) DSMB members will determine that the events are serious enough to notify all participants enrolled and any future eligible participants about the nature of the event and expected consequences for remaining enrolled or initiating enrollment; and (c) DSMB members will determine that events are not serious enough to notify participants and potential enrollees, and the study enrollment and follow-up will proceed as outlined in the study protocol.

## Trial status

Aim 1 (longitudinal cohort) recruitment began in May 2022 and is ongoing. Aim 2 (intervention) recruitment is planned for spring 2023 and is expected to be completed in spring 2024. Aim 3 (process evaluation) data collection will occur after sufficient completion of the 6-month assessment in Aim 2. Final results are anticipated in fall 2025.

## Discussion

The outlined research seeks to advance our understanding of how food insecurity impacts the development of cardiometabolic comorbidities among PWH and how interventions for food insecurity may alleviate relevant comorbidities. Given the growing interest among health systems in addressing food insecurity as a routine part of clinical practice, if the intervention is found to be efficacious, it could be broadly disseminated across HIV clinical care settings.

## Data Availability

De-identified data and associated documentation will be available from the Principal Investigators under a data-sharing agreement with users that provides for a commitment to using the data for research purposes, a commitment to securing the data using appropriate computer technology, and a commitment to destroying or returning the data after analyses are completed. Informed consent forms are available from the corresponding author by request.

## Abbreviations

ART: Antiretroviral therapy
EHR: Electronic health record
HOMA-IR: Homeostatic model assessment of insulin resistance
IRB: Institutional Review Board
PWH: People living with HIV
SNAP: Supplemental Nutrition Assistance Program
SDH: Social determinants of health
TANF: Temporary Assistance for Needy Families
T2DM: Type 2 diabetes mellitus
WIC: Special Supplemental Nutrition Program for Women, Infants, and Children
